# Efficacy of the SOAR knee health program: protocol for a two-arm stepped-wedge randomized delayed-controlled trial

**DOI:** 10.1186/s12891-022-05019-z

**Published:** 2022-01-25

**Keywords:** Anterior cruciate ligament, Knee trauma, Post-traumatic osteoarthritis, Physiotherapy

## Abstract

**Background:**

Knee trauma permanently elevates one’s risk for knee osteoarthritis. Despite this, people at-risk of post-traumatic knee osteoarthritis rarely seek or receive care, and accessible and efficacious interventions to promote knee health after injury are lacking. Exercise can ameliorate some mechanisms and independent risk factors for osteoarthritis and, education and action-planning improve adherence to exercise and promote healthy behaviours.

**Methods:**

To assess the efficacy of a virtually-delivered, physiotherapist-guided exercise-based program (SOAR) to improve knee health in persons discharged from care after an activity-related knee injury, 70 people (16–35 years of age, 12–48 months post-injury) in Vancouver Canada will be recruited for a two-arm step-wedged assessor-blinded delayed-control randomized trial. Participants will be randomly allocated to receive the intervention immediately or after a 10-week delay. The program consists of 1) one-time Knee Camp (group education, 1:1 individualized exercise and activity goal-setting); 2) weekly individualized home-based exercise and activity program with tracking, and; 3) weekly 1:1 physiotherapy-guided action-planning with optional group exercise class. Outcomes will be measured at baseline, 9- (primary endpoint), and 18-weeks. The primary outcome is 9-week change in knee extension strength (normalized peak concentric torque; isokinetic dynamometer). Secondary outcomes include 9-week change in moderate-to-vigorous physical activity (accelerometer) and self-reported knee-related quality-of-life (Knee injury and OA Outcome Score subscale) and self-efficacy (Knee Self Efficacy Scale). Exploratory outcomes include 18-week change in primary and secondary outcomes, and 9- and 18- week change in other components of knee extensor and flexor muscle function, hop function, and self-reported symptoms, function, physical activity, social support, perceived self-care and kinesiophobia. Secondary study objectives will assess the feasibility of a future hybrid effectiveness-implementation trial protocol, determine the optimal intervention length, and explore stakeholder experiences.

**Discussion:**

This study will assess the efficacy of a novel, virtually-delivered, physiotherapist-guided exercise-based program to optimize knee health in persons at increased risk of osteoarthritis due to a past knee injury. Findings will provide valuable information to inform the management of osteoarthritis risk after knee trauma and the conduct of a future effectiveness-implementation trial.

**Trial registration:**

Clinicaltrials.gov reference: NTC04956393. Registered August 5, 2021, https://clinicaltrials.gov/ct2/show/NCT04956393?term=SOAR&cond=osteoarthritis&cntry=CA&city=Vancouver&draw=2&rank=1

**Supplementary Information:**

The online version contains supplementary material available at 10.1186/s12891-022-05019-z.

## Background

The Global Burden of Disease Study reports osteoarthritis (OA) as one of the fastest growing and burdensome conditions worldwide, [1] driven primarily by OA of the knee [2]. Given there is no cure for OA disease (articular and periarticular pathology), and only modestly effective treatments for OA illness (pain, disability, reduced quality-of-life; QoL), there is a desperate need for effective and accessible prevention interventions that strategically target at-risk populations [3].

Knee trauma is associated with a 6-fold increased risk of radiographic OA by 11 years, [4] and 6-fold increased risk of arthroplasty [5]. OA risk varies by injury type with cruciate ligament, meniscal, fracture, dislocation and collateral ligament injuries associated with 5-fold or higher risk [4]. Knee trauma is most prevalent in persons aged 16–35 years, and most commonly activity related [6]. Due to a relative young age at injury, people with knee trauma develop OA earlier compared to those without trauma, resulting in greater years lived with disability and reduced QoL.

The elevated risk for OA after trauma is driven by altered cartilage metabolism, [7] altered loading, [8] and inflammation [9]. We have also shown that youth with knee trauma up to 10-years previous have more independent OA risk factors (i.e., quadricep weakness, inactivity, adiposity) [10–12] than uninjured peers. Despite carrying these modifiable risk factors, people at-risk of OA after trauma are rarely aware of their risk, nor do they seek, or receive care to manage this risk [13, 14].

Exercise ameliorates several mechanisms (altered loading, [15] inflammation [16]) and independent risk factors (muscle weakness, [17] inactivity, [18] adiposity [19]) for OA. Despite this, the current standard of care after discharge from knee trauma treatment is no care, and the value of exercise-based activities to modify OA risk factors after trauma is unclear [20]. Given that knee trauma permanently elevates OA risk, strategies that enhance self-management, exercise adherence, and healthy lifestyles, such as informational support and action-planning are valuable adjuncts to exercise [21–23].

SOAR (Stop OsteoARthritis) is a virtually-delivered, physiotherapist (PT)-guided knee health program. SOAR aims to increase the capacity of persons living with an increased risk of OA due to an activity-related knee injury to self-manage their knee health and knee OA risk. The program was developed alongside patient and clinician partners, and is based on past research, [10, 12, 24–26] clinical practice guidelines, [17] guidance for Developing and Evaluating Complex Interventions, [27] and is consistent with patient-centered care, [28] shared decision making [29] and behaviour change theory [30]. Recently we have established the feasibility of the SOAR program [31]. Prior to determining the effectiveness of SOAR it needs to be assessed in an ideal (efficacy) setting.

## Methods

### Aim

The primary objective of this study is to assess the efficacy of an 8-week SOAR program to improve knee extensor muscle strength, moderate-to-vigorous physical activity (MVPA), self-reported knee-related QoL, and knee-specific self-efficacy in people discharged from regular care after a sport or recreational-related knee trauma. Additional objectives are to evaluate the feasibility of a future hybrid effectiveness-implementation randomized controlled trial (RCT) protocol, determine the optimal intervention length, and explore stakeholder experiences.

### Study design and setting

This is a proof-of-concept, two-armed, open-label, randomized delayed control trial [32] with embedded 1:1 interviews. In this design, randomization determines when the intervention is provided (immediate or 9-week delay). A delayed-control is appropriate as the standard of care after discharge from knee trauma care is no care, and the intervention is beneficial and low risk [33, 34].

The study is guided by the Standard Protocol Items: Recommendations for Intervention Trials, [35] and Standards for Reporting Qualitative Research [36]. Protocol reporting follows the Standard Protocol Items: Recommendations for Intervention Trials, while trial reporting will follow the Consolidated Standards of Reporting Trials statement [37] and Consensus on Exercise Reporting Template [38]. Protocol feasibility assessments will be guided by Bowen et al. [39] and Thabane et al. [32] The research will be conducted at the University of British Columbia (UBC) and Arthritis Research Canada, in Vancouver, Canada between December 2021 and December 2022. The study is approved by the UBC Clinical Research Ethics Board (REB #H21–01491) and all participants will provide informed consent and complete a Physical Activity Readiness questionnaire (PAR-Q,2002) prior to testing [40].

### Participants

Both persons who have experienced a past sport or recreational-related knee injury and physical therapists will be recruited during this study. Knee injury participants will include a convenience sample of individuals who are at least 12-, but not more that 48-months, past an activity-related knee injury, 16–35 years of age, and not receiving on-going healthcare for their knee. A 12–48-month post-injury period is consistent with completion of knee injury rehabilitation (typically ≤12-months), [41] precedes radiographic OA, [4] and has been identified by patient partners as an opportune time. Activity-related knee injury is defined as self-reported knee trauma requiring medical consult that disrupted activity participation on more than one occasion [42]. Persons will be excluded if they have OA illness (i.e., movement related joint pain + morning stiffness < 30 min + functional limits with either crepitus, or motion loss per the EULAR criteria) [43]; inflammatory arthritis or systemic condition; leg injury, surgery, or injection in the past 6-months; pregnancy; no email address or daily access to a computer with internet; or refuse to wear an activity tracker.

Musculoskeletal PTs will also be enrolled to deliver the intervention to participants with a past knee injury. PT participants must be registered to practice in the province of British Columbia, Canada, able to communicate in English, be willing to complete Brief Action Planning (BAP) and SOAR program training, and have daily access to a computer with internet service.

### Recruitment

Participants with a previous knee injury will be recruited through the study’s social media accounts and established local PT clinics and sport organizations. PTs will be recruited through the British Columbia physical therapy research Collaboration Registry go.library.ubc.ca/9852gp and through word of mouth.

### Sample size

The sample size of knee injured participants is based on detecting a meaningful change in normalized peak knee extensor torque (Nm/kg) between study groups over 8-weeks, with 25% attrition. Bodkin et al. [44] reports that a gain in normalized knee extensor torque of 0.22 Nm/kg [44] discriminates people who achieve clinically relevant gains in self-reported knee function, 6–9 months post-trauma. To detect a mean change of 0.22 Nm/kg in the immediate intervention study group assuming no change in the delayed intervention study group, and a common standard deviation (0.25 Nm/kg), [11] a sample of 42 participants (21/group) is needed (two-sided test, 1-β = 0.8, α =0.05). Recruitment of 70 participants (35/group) allows for 25% attrition.

### Procedures

Figure 1 outlines the study phases for participants with a past knee injury. Interested persons will be directed to an online screening survey (Qualtrics XM, US) and those potentially eligible will be emailed study information and scheduled for a videoconferencing interview to confirm eligibility. Eligible persons will receive an URL to an electronic consent form located on a data management platform (REDCap 10.9.4, Vanderbilt University, US). After consenting, participants will complete baseline testing and be randomly allocated to study group (see below). The immediate study group (IG) will be complete an 8-week (weeks 1–8) SOAR program (Knee Camp, home-based exercise-therapy and physical activity with tracking, weekly 1:1 PT counseling sessions, and optional weekly group-based exercise classes) followed by an additional 8 weeks (weeks 10–17) of home-based exercise-therapy and physical activity with tracking, weekly 1:1 PT counseling sessions, and optional weekly group-based exercise classes. In contrast, after a 10-week delay, the delayed study group (DG) will complete an 8-week (weeks 10–17) SOAR program (Knee Camp, home-based exercise-therapy and physical activity with tracking, weekly 1:1 PT counseling sessions, and optional weekly group-based exercise classes). Knee injury participant outcomes will be evaluated at baseline (T0), 9-weeks (T1-primary endpoint to assess efficacy), and 18-weeks (T2- endpoint to inform optimal intervention length).

**Fig. 1 Fig1:**
[figure not shown]
Overview of knee injury participant flow through the study

Figure 2 outlines the study phases for the PT participants. Interested PTs will attend an online information session and then send an email to research team to express their interest. After a videoconferencing interview to confirm eligibility PTs will receive an URL to an electronic consent form located on a data management platform (REDCap 10.9.4, Vanderbilt University, US). After consenting, PT will complete baseline testing (online questionnaires), training and then will be randomly assigned to knee injury participants (see below). PT outcomes will be evaluated prior to training (baseline) immediately after training, and after they have delivered the SOAR program to all knee injury participants that they have been assigned in the study.

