### Statistical analyses

Descriptive statistics will be calculated for demographic and potential confounding variables (i.e., injury type, time since injury, prior or subsequent injury, prior treatment), and observed differences will be considered when interpreting findings, and during the design of a future hybrid effectiveness-implementation RCT. Randomization integrity will be monitored. Mean changes in all outcomes between T0 and T1, and T1 and T2 will be described by study group and sex (knee extension torque) or gender (physical activity, KOOS, KSES).

We will conduct intent-to-treat analyses (compare outcomes according to randomized study groups, regardless of intervention adherence). Missing outcome data due to missed visits or dropouts will be handled using multiple imputations of missing values. Generalized linear mixed-effects regression models for longitudinal data (95%CI), controlling for blocking effect, will estimate the effect of the 8-week intervention (IG T1-T0 versus DG T1-T0, and DG T2-T1 versus T1-T0) and delay (IG T1-T0 versus DG T2-T1) for the primary outcome (knee extension torque change; Fig. 3).

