**Fig. 3 Fig3:**
[figure not shown]
Analysis contrasts

We will conduct three exploratory analyses to guide design of the future hybrid effectiveness-implementation RCT. To inform primary outcome choice individual generalized linear mixed-effects regression models for longitudinal data (95%CI), controlled for blocking effect, will explore the effect of the 8-week program (IG T1-T0 versus DG T1-T0) on MVPA time, KOOS function in sport/recreation sub-scale, and KSES considering gender. To inform the most relevant muscle function outcome individual linear regression (95%CI) models, adjusted for age and sex, will compare the association between the change in knee extensor muscle function torque, power, and rate of force development over the 8-week intervention with the KOOS_4_. To inform optimal intervention length, a longitudinal mixed-effects model will examine the intervention effect at 18-weeks. This model will include the following fixed effects indicators: 1) study group (i.e., IG or DG) to account for baseline difference; 2) follow-up point (i.e., T1 or T2) to account for secular trend, and; 3) time since intervention initiation (i.e., 18- or 9-weeks) to estimate effects after these time intervals. The model will also include participant-specific random effects to account for repeated measures. As type II error is a greater concern in proof-of-concept trials than type I, we will not adjust for multiple comparisons [81].

Interview recordings will be transcribed verbatim and de-identified. Using a constant comparative approach [77] data will be coded and categories developed by comparing and determining meaningful patterns across codes. High-order themes will illuminate the relationship between categories. We will look for uniqueness in experience by gender. If gender-based themes are identified, data will be reanalyzed with a gender lens. Analysis credibility and trustworthiness will be fostered through data immersion, reflexive journaling, field notes, memoing and regular research team discussions of coding, early concepts and developing themes. A detailed audit of analytic decisions will be kept [82].

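### The stated primary model has no therapist term although the immediate group is nested in physiotherapists from T0 to T1; if the therapist ICC exceeds 0, its confidence interval will be too narrow

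*Protocol article*

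**What the plan says.** All references are to the protocol article.

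- **Therapist assignment (Procedures).** After training, physiotherapists "then will be randomly assigned to knee injury participants". Their own outcomes are assessed once they have delivered the programme to all participants assigned to them, so a caseload is more than one person.
- **Therapist role (Knee camp; Weekly PT-guided exercise-therapy and physical activity action-planning).** The physiotherapist does the individual knee exam, sets exercise and activity goals with the participant, and revises them in weekly one-to-one sessions.
- **Timing (Procedures).** From T0 to T1 the IG receives the programme and the DG waits.
- **Primary model (Statistical analyses).** "Generalized linear mixed-effects regression models for longitudinal data (95%CI), controlling for blocking effect". No other design term is named for this model, and its random effects are not listed.
- **18-week exploratory model (Statistical analyses).** It lists fixed effects for group, follow-up point and time since initiation, and adds: "The model will also include participant-specific random effects to account for repeated measures".
- **Sample size.** "To detect a mean change of 0.22 Nm/kg in the immediate intervention study group", with no change in the DG and "a common standard deviation (0.25 Nm/kg"), "a sample of 42 participants (21/group) is needed" ("two-sided test, 1-β = 0.8, α =0.05"). No ICC or design effect appears.

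**The concern.** Participants who share a physiotherapist share that person's skill in setting and progressing exercise, so their strength gains may be correlated. Assigning physiotherapists at random removes selection into caseloads but does not remove that correlation. In the primary contrast (IG T1-T0 against DG T1-T0) the correlation can arise in one arm only.

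The blocking effect does not cover it. In the section on randomization allocation, blocks are the variable-size randomization blocks within sex strata, and the physiotherapist is not a stratification factor.

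At stake is the validity of the interval and test for the primary outcome. With any positive therapist ICC, an analysis that treats IG participants as independent reports too small a standard error.

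**Working it through.** **Inputs from the Sample size section.** Difference 0.22 Nm/kg, SD 0.25 Nm/kg, two-sided alpha 0.05, power 0.80, 35 recruited per group, 25% attrition (35 × 0.75 = 26.25, so about 26 per group).

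**Assumptions.** The total number of physiotherapists is not stated. The section on perspectives of PT participants plans interviews with about 7, so k = 7 is used. No ICC is given; the range is 0.01 to 0.10. Caseloads are taken as equal.

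**Step 1: reproduce the plan's figure.** Under independence, n per group = 2 × (1.960 + 0.842)² × 0.25² / 0.22² = 20.3, rounded up to 21, total 42. This matches the plan. The t-test version gives 22 per group, total 44.

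**Step 2: add clustering in the IG only.**

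- Caseload m = n/k. With k = 7, m = 26/7 = 3.71 or 35/7 = 5.
- IG design effect DE = 1 + (m − 1) × ICC.
- The variance of the group difference is multiplied by (DE + 1)/2, and the standard error by r = √[(DE + 1)/2].
- Type I error of the independence analysis = 2 × [1 − Φ(1.96/r)].
- Power with the correct standard error = Φ(0.22/SE − 1.96), where SE = r × 0.25 × √(2/n).

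Example, n = 26 and ICC 0.05: DE = 1 + 2.71 × 0.05 = 1.136; r = √1.068 = 1.033; SE = 1.033 × 0.0693 = 0.0716. The 95% half-width goes from 0.136 to 0.140 Nm/kg.

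| n per group | ICC | DE | SE larger by | Type I error, formula | Type I error, simulated | Power |
|---|---|---|---|---|---|---|
| 26 | 0 | 1 | 0% | 5.0% | 4.9% | 88.7% |
| 26 | 0.01 | 1.03 | 0.7% | 5.2% | – | 88.3% |
| 26 | 0.05 | 1.14 | 3.3% | 5.8% | 5.9% | 86.7% |
| 26 | 0.10 | 1.27 | 6.6% | 6.6% | 6.7% | 84.5% |
| 35 | 0 | 1 | 0% | 5.0% | 4.8% | 95.7% |
| 35 | 0.01 | 1.04 | 1.0% | 5.2% | – | 95.4% |
| 35 | 0.05 | 1.20 | 4.9% | 6.2% | 6.1% | 93.9% |
| 35 | 0.10 | 1.40 | 9.5% | 7.4% | 7.3% | 91.9% |

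The simulated column comes from 40,000 trials per setting, analysed without a therapist term. The rows for 26 and 35 bracket the case in which all randomized participants stay in the analysis through multiple imputation.

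**Step 3: the sample size.** With 7 physiotherapists, 80% power needs 42, 44 and 46 evaluable participants at ICC 0.01, 0.05 and 0.10. After division by 0.75 that is 56, 59 and 62 recruited, all below the planned 70.

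**The case against.** The strongest reply is that silence is being read as a decision. The primary model is called a mixed-effects model and its random effects are not listed. The sentence on participant-specific random effects belongs to the exploratory 18-week model, and its wording does not exclude other terms. A journal article condenses, and an unseen SAP could add a therapist effect. This stands: a reader might infer that the trial has decided to ignore therapists, and the article does not show that. What remains is that the article does name the design feature to be controlled, and it is the wrong one for this purpose. The one model whose terms are set out has no therapist term either, and the sample size reproduces only under independence.

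Other readings go further than the documents allow:

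- *The interval is too narrow as a matter of fact.* This needs an ICC above 0, which the documents do not give. At ICC 0 the simulated error rate is about 5%.
- *The trial is underpowered.* It is not, at the planned recruitment. Only at the bare minimum of 21 per group does power slip below 80% (79.5% at ICC 0.05 and 77.6% at 0.10 with 7 physiotherapists). With 4 physiotherapists, 26 per group and ICC 0.10 it is still 80.2%.
- *The inflation is large.* With 4 physiotherapists and 35 per group, type I error reaches 7.4% at ICC 0.05 and 9.8% at 0.10. But about 7 are to be interviewed, so 4 is an unlikely edge.
- *The trial throws away its therapist variance estimate.* Nothing in the article prevents estimating it. Equally, the article does not say that physiotherapist identity will be an analysis variable.

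It can also be said that this is a proof-of-concept trial that ranks type II error above type I. The article uses that argument only to justify making no adjustment for multiple comparisons. It does not extend to a misstated standard error in the primary contrast.

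**Conclusion.** The point holds in conditional form. The primary model as stated and the sample size take no account of therapist clustering, which between T0 and T1 exists in the IG only. If the therapist ICC exceeds 0, the primary interval will be too narrow. Under the assumptions of 7 physiotherapists, equal caseloads, 26 to 35 per group and ICC 0.01 to 0.10, the true standard error is about 1% to 10% larger and type I error about 5.2% to 7.3%. A middle case (ICC 0.05, 26 per group) gives about 3% and 5.8%.

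The effect is modest and concerns interval validity, not power. Dividing 42 by 0.75 gives 56, so the 70 planned leave a surplus that absorbs the loss of power; that surplus does not correct an understated standard error. Shared Knee Camp sessions and group classes could add some further correlation, which is not quantified here.

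**What to change.** State in the primary model, or at minimum in a prespecified sensitivity analysis, a therapist random effect that applies only to programme-exposed records: IG from T1 and DG at T2. Use Kenward-Roger or Satterthwaite degrees of freedom, because therapists are few. Keep physiotherapist identity in the analysis dataset, and report the therapist ICC with its interval for use in planning the later effectiveness-implementation trial.

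The cost is analysis wording and one retained variable; recruitment need not change. The price is a slightly wider interval and a variance component that will be imprecise with about 7 therapists, so the ICC should be presented as a rough guide.
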